## Abstract

**Background:**

Approximately half of preterm births are attributable to maternal infections, which are commonly undetected and untreated in low-income settings. Our primary aim is to determine the impact of early pregnancy screening and treatment of maternal genitourinary tract infections on the incidence of preterm live birth in Sylhet, Bangladesh. We will also assess the effect on other adverse pregnancy outcomes, including preterm birth (stillbirth and live birth), late miscarriage, maternal morbidity, and early onset neonatal sepsis.

**Methods/Design:**

We are conducting a cluster randomized controlled trial that will enroll 10,000 pregnant women in Sylhet district in rural northeastern Bangladesh. Twenty-four clusters, each with ~4000 population (120 pregnant women/year) and served by a community health worker (CHW), are randomized to: 1) the control arm, which provides routine antenatal and postnatal home-based care, or 2) the intervention arm, which includes routine antenatal and postnatal home-based care plus screening and treatment of pregnant women between 13 and 19 weeks of gestation for abnormal vaginal flora (AVF) and urinary tract infection (UTI). CHWs conduct monthly pregnancy surveillance, make 2 antenatal and 4 postnatal home visits for all enrolled pregnant women and newborns, and refer mothers or newborns with symptoms of serious illness to the government sub-district hospital. In the intervention clusters, CHWs perform home-based screening of AVF and UTI. Self-collected vaginal swabs are plated on slides, which are Gram stained and Nugent scored. Women with AVF (Nugent score ≥4) are treated with oral clindamycin, rescreened and retreated, if needed, after 3 weeks. Urine culture is performed and UTI treated with nitrofurantoin. Repeat urine culture is performed after 1 week for test of cure. Gestational age is determined by maternal report of last menstrual period at study enrollment using prospectively completed study calendars, and in a subset by early (<20 week) ultrasound. CHWs prospectively collect data on all pregnancy outcomes, maternal and neonatal morbidity and mortality.

**Implications/Discussion:**

Findings will enhance our understanding of the burden of AVF and UTI in rural Bangladesh, the impact of a maternal screening-treatment program for genitourinary tract infections on perinatal health, and help formulate public health recommendations for infection screening in pregnancy in low-resource settings.

**Trial registration:**

The study was registered on ClinicalTrials.gov:NCT01572532 on December 15, 2011. The study was funded by NICHD: R01HD066156.

## Background

About 15 million babies are born preterm (born <37 weeks of gestation) annually [1], and preterm birth is the leading cause of neonatal and under-5 child mortality globally, accounting for one million neonatal deaths annually [2, 3]. Eleven million preterm births and the vast majority of deaths due to preterm birth complications occur in low-income countries, where there are limited resources and capacity for prevention and management. One third of preterm survivors suffer from severe long term neurological disabilities (e.g., cerebral palsy or mental retardation) [4, 5], and preterm infants carry increased risk of behavioral problems, school learning difficulties, chronic lung disease, retinopathy of prematurity, hearing impairment, and lower growth attainment [5]. Few interventions effectively prevent preterm birth [6], and the incidence of preterm birth is rising, in both low- and high-income countries [1, 7–11].

Treatment of maternal infections is a critical target for the prevention of preterm birth, particularly in low-income settings. Genitourinary tract infections may affect up to 41 % of women of reproductive age globally, and as many as 60–80 % of these infections in pregnancy are asymptomatic [12]. Maternal genitourinary tract infections have been significantly associated with a wide range of adverse perinatal and maternal outcomes, including miscarriage, stillbirth, preterm birth, fetal growth restriction, neonatal and puerperal sepsis, neonatal encephalopathy and neonatal and maternal mortality [13–16]. In developing countries where antenatal care coverage is limited [17], maternal infections are inadequately diagnosed and treated. Lower genital tract infections may ascend the reproductive tract and seed the amniotic cavity, which can trigger an inflammatory cascade eventually resulting in a number of adverse outcomes including preterm birth, chorioamnionitis, fetal growth restriction, stillbirth, puerperal sepsis and early onset sepsis. Maternal infection accounts for an estimated 50 % of preterm births [18], thus timely diagnosis and treatment of maternal infections is a prime target for the prevention of preterm birth, as well as other adverse pregnancy outcomes [19].

Abnormal vaginal flora (AVF), including bacterial vaginosis (BV), is the most prevalent vaginal infection in pregnancy, and is significantly associated with increased risk of preterm birth. AVF is triggered by an imbalance in the concentrations of endogenous vaginal microflora—a reduction in normal lactobacilli and the opportunistic overgrowth of *Gardnerella vaginalis* and other anaerobic organisms [20, 21]. Nugent et al. defined a scoring system (0–10) for vaginal flora based on a weighted combination of the relative concentrations of 3 bacterial morphotypes: *Lactobacillus*, *Gardnerella* or *Bacteroides*, and curved gram-variable rods (*Mobiluncus*) [22] [BV = Nugent score ≥ 7, intermediate flora: Nugent score 4–6, and AVF: Nugent score ≥4]. In a meta-analysis of 32 studies, asymptomatic BV was associated with a 6.32 times elevated risk of late miscarriage (95 % CI 3.65–10.94) and 2.16 times increased risk of preterm birth (95 % CI 1.56–3.00) [23]. Furthermore, intermediate vaginal flora is a heterogeneous condition which comprises ~15 % of all AVF [24], and has been associated with elevated risk of preterm birth and neonatal infections [25–28]. Among women with a prior history of preterm birth, Hauth and colleagues found that screening and treatment of asymptomatic BV with metronidazole and erythromycin at 22 weeks gestation significantly reduced the incidence of preterm birth from 46 to 31 % in the treatment group [29]. In the multi-center National Institute of Child Health & Human Development (NICHD) BV trial, 1953 average-risk women with asymptomatic BV between 16 and 24 weeks of gestation were randomized to receive two doses of metronidazole (2 g) or placebo. Treatment, however, did not significantly affect preterm delivery or other adverse perinatal outcomes [30]. In a more recent trial, Ugwumadu et al. reported that early (12–22 weeks of gestation) screening and treatment for AVF with 5 days of oral clindamycin resulted in a significant reduction in spontaneous preterm birth rate (12 % in placebo vs. 5 % in treatment group) and late miscarriage (13–24 weeks; 4 % in placebo vs. 1 % in treatment group) [24]. Lamont et al. randomized women with AVF between 13 and 20 weeks gestation to receive intravaginal clindamycin cream or placebo between 13 and 20 weeks gestation, and found that among infected women, there was a significant reduction in preterm birth incidence (10 % in control vs. 4 % in treatment group) [31]. Potential explanations for the treatment effect in the two latter trials may include: 1) the earlier timing of treatment, prior to the amniotic membranes sealing the uterus at 20 weeks [32], which may prevent early ascension of bacteria into the intrauterine cavity; 2) antibiotic choice: 5–7 day course of clindamycin, which has greater activity against *Mobiluncus* and atypical *Mycoplasma* species vs. 2 days of metronidazole [33]; and 3) treatment of AVF in Ugwumadu et al. and Lamont et al. vs. treatment of BV only in the average-risk NICHD trial. A Cochrane meta-analysis including 15 trials (n=5888 women) concluded that BV treatment across all gestational ages did not significantly reduce preterm birth, largely due to heterogeneity in definition, timing of treatment and choice of antibiotic [33]. However, the risk of preterm birth was significantly reduced by treatment of BV at <20 weeks gestation (5 trials in 2387 women; OR 0.63, 95 % CI 0.48–0.84) and treatment of AVF (2 trials, 894 women; OR 0.51, 95 % CI 0.32–0.81). Thus, in low-resource settings such as rural Bangladesh, where BV and preterm birth are prevalent, treatment of AVF in early pregnancy may hold promise in reducing the incidence of preterm birth. Evaluation in a well-conducted population-based randomized trial is needed.

Urinary tract infection (UTI) is also prevalent in pregnancy and associated with preterm birth. Uropathogens tend to be gram-negative bacteria with virulence factors and endotoxins, which may trigger the inflammatory cascade and preterm delivery. The prevalence of asymptomatic bactiuria in pregnancy may range from 7 % to as high as 86.6 % [34, 35]. Approximately 30 % of women with untreated bactiuria develop pyelonephritis [36], and before the era of antibiotics, 30–50 % of women with pyelonephritis delivered preterm [37]. In an early meta-analysis by Romero et al., asymptomatic bactiuria carried a 2-fold elevated risk of preterm delivery (95 % CI 1.43–2.77) [38]. In the Cardiff Birth Survey, asymptomatic bactiuria was not associated with all preterm births (OR 1.2, 95 % CI 0.9–1.5); however there was a significant association with medically indicated preterm birth (OR 2.0; 95 % CI 1.5–2.8) [39]. In a meta-analysis of randomized clinical trials for asymptomatic bactiuria, antibiotic treatment reduced the risk of low birth weight (RR 0.56, 95 % CI 0.43–0.73; *n* = 8 studies) [38], however there are inadequate data on the effect on preterm birth.

### Study site and population

The Maternal Infection Screening and Treatment (MIST) study is being conducted in the Projahnmo research site in two sub-districts (*upazillas*; Zakiganj and Khanaighat) of Sylhet District in Bangladesh (Fig. 1, Map). Projahnmo is a collaboration of the Ministry of Health and Family Welfare (MOHFW) of the Government of Bangladesh, the International Centre for Diarrhoeal Disease Research, Bangladesh (iccdr,b), Shimantik (a non-governmental organization), Child Health Research Foundation, Brigham and Women’s Hospital (Harvard Medical School), and the Johns Hopkins Bloomberg School of Public Health. The estimated population of the MIST study area is about 100,000. The burden of prematurity, neonatal sepsis, neonatal death, and stillbirth is high in this population (preterm birth rate: 22 %, clinical neonatal sepsis: 9.9 %, neonatal mortality rate: 28/1000 live births, stillbirth rate: 38/1000 births) [40, 41]. Health services in Bangladesh are provided by the MOHFW, NGOs and private providers. In the government sector, two community-based workers, a family welfare assistant and a health assistant together serve a population of 6000–7000. First level outpatient clinics, called Health and Family Welfare Centres, serve a population of about 25,000, with one clinic per union (lowest local government entity in Bangladesh). Sub-district hospitals with both inpatient and outpatient facilities serve a population of about 250,000.

**Fig. 1 Fig1:**
[figure not shown]
Map of Sylhet District, Bangladesh and unions participating in the Projahnmo MIST trial

The study area is served by 24 project CHWs, who are women with at least a 10th grade education, are residents of the study community, and have received 6 weeks of training on basic maternal and newborn care. Within each CHW cluster area, there are additionally Village Health Workers (VHWs), one in each village with a population of ~1000. Each cluster area is assigned to 1 CHW and 4–5 VHWs to serve an estimated 120 pregnancies and 116 live births annually; this is feasible because the trial area has very high population density, and the same ratio of population to CHWs/VHWs has been used in our previous and current studies in Sylhet.

We conducted a complete census and socioeconomic survey of the study population in 2009 and continue to conduct health and demographic surveillance every two months. All households and women of childbearing age have unique current and permanent identification numbers, which allows individual tracking and longitudinal follow-up.

### Pregnancy surveillance, eligibility, and enrollment (Fig. 2)

**Fig. 2 Fig2:**
[figure not shown]
Trial design flowchart

All women who become pregnant in the study area are potentially eligible to participate in the trial. Prior to the start of the study, all women of reproductive age (15–49 yo) in the study area were provided study calendars with instructions and training by CHWs to prospectively circle the first day of each menstrual cycle. VHWs conduct monthly pregnancy surveillance visits where mothers are asked if their last menstrual period (LMP) was greater than 4 weeks ago. If LMP was >4 weeks, a CHW conducts a home visit to perform a urine pregnancy test. Enrollment may begin as soon as 5 weeks gestation and continues until 19 weeks gestation. At the time a missed period is detected during screening for study eligibility. Subjects are excluded from the study if they have no or uncertain recall of LMP (due to lactational amenorrhea, recent discontinuation of contraceptive or irregular menses), LMP >19 weeks, history of irregular bleeding due to injectable Depo-Provera, or self-reported history of severe chronic disease based on a medical history checklist. Participants are enrolled after final eligibility is confirmed by the CHW and oral consent is obtained.

### Basic antenatal-postpartum care package

In all study areas, CHWs provide basic antenatal and postpartum care. This consists of two antenatal home visits (13–19 weeks and 28–32 weeks of gestation) and four postnatal home visits (1st, 3rd, 7th, and 28th day of life) to all enrolled pregnant women. During antenatal home visits, CHWs provide: counseling on birth and newborn care preparedness (importance of antenatal check up, use of a skilled/trained birth attendant, essential newborn care, danger signs, care seeking, birth spacing), demonstrations (hand washing, cord cutting, immediate newborn care), facilitation (emergency savings, selection of birth attendant and newborn care person), supply (clean delivery kit, iron folate tablets) and referral (for routine antenatal care, tetanus toxoid immunization, maternal danger signs). Postnatal visit components include: counseling (maternal and newborn danger signs, essential newborn care, and exclusive breast feeding), assessment of the newborn (morbidity and breastfeeding), referral (for newborn and maternal danger signs, postpartum contraceptive methods), demonstration/support (breastfeeding techniques) and supply (contraceptives).

### Randomization

The units of randomization in this trial are the 24 CHW areas, each comprising several adjacent villages. Allocation to the intervention vs. control arms was done via a restricted randomization procedure. All $$ \left(\begin{array}{c}\hfill 24\hfill \\ {}\hfill 12\hfill \end{array}\right) $$ possible randomization sequences were generated where each sequence allocated 12 of the CHW areas to either intervention or control. Using data on births and preterm status from our prior study in this area [42], we restricted the set of eligible sequences to those where intervention vs. control ratios of predicted preterm birth and predicted total births were within 0.975 to 1.025. An additional criterion for retaining a sequence as eligible was that the 13 CHW areas that had participated in a prior study on birth spacing (“The Health Fertility Study”) were allocated equally to intervention and control (i.e. 6 and 7 or 7 and 6). Among the 2,704,156 sequences, 164 sequences met the criteria, from which a single sequence was randomly selected. Workers and participants in the study are not blinded to the intervention group but are not aware of the study aims/hypotheses.

### Screening and treatment intervention

The screening and treatment intervention is provided to all pregnant women enrolled in the intervention clusters. Furthermore, to examine the comparability of baseline infection prevalence between intervention and control areas, a random 10 % of mothers enrolled in the control arm are selected to receive the screening and treatment intervention. To select the 10 % of mothers from control areas, each CHW initially randomly selected a number between 1 and 10 which indicated the starting number of the women in her area to receive the intervention. From that starting point every 10th enrolled mother was included in the group to receive the screening and treatment intervention. The sample size was not adjusted for this allocation.

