#### Preterm live birth

Preterm live birth is defined as a baby born alive <37 weeks gestation defined by LMP. Early preterm live birth is defined as a baby born alive <34 weeks gestation defined by LMP. The denominator for preterm live birth rates is all live births.

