### Sample size and analysis

In order to calculate the sample size, we first hypothesized that a population-level reduction in the preterm rate in the range of 15–20 % would be of public health importance, given the importance of the outcome and the level of complexity of any future scaled- up programmatic implementation of the intervention. Once we established this desired effect size range, we worked through a series of calculations (with corresponding assumptions) to determine the number of babies required to achieve sufficient power (i.e. 80 %) for a population-level reduction in this range (i.e. 15–20 %).

Given that the intervention is directed only at a subset of the population, we first estimated the proportion of preterm birth among both infected and non-infected women. Estimation of these proportions requires three parameters:The proportion of preterm in the population: we estimated this to be 20 %, based on our prior data from this population [51].The proportion of women in the intervention clusters that actually receive treatment under the universal screening program, or equivalently an estimate of the total proportion of women with UTI and/or AVF (Nugent ≥4).The ratio of preterm birth risk among infected and non-infected women; we estimated this ratio to be 2.5 from the literature.

From previous data and the literature, we estimated that about 15 % of women in this setting have either AVF, UTI, or both. Among those with AVF, some will fall into the intermediate flora score range (Nugent score 4–6) and some into the BV scoring range (Nugent score 7–10). Our best estimates of the relative proportions in these two subgroups was approximately 85 % within the BV (Nugent 7–10) range, with the remaining 15 % of women with AVF falling within the intermediate flora scoring range (Nugent 4–6) [24]. We based our prevalence estimates and treatment effect size on prior studies of similar screening and treatment programs for **all abnormal vaginal flora** (Nugent scores ≥4).

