### Analysis

Interim (i.e. for DSMB analyses) and final analyses will follow the same protocol. First, we will present descriptive information on the recruitment, enrollment, and follow up of women and their newborns (i.e. a participant flowchart). We will then assess characteristics of the enrolled pregnancies to determine the extent to which our randomization procedure achieved comparability; these characteristics will include maternal, paternal, household, and socio-economic variables. For clusters allocated to the intervention arm we will describe the coverage of the screening and treatment intervention, including the distribution of time (i.e. gestational age) at screening, results of the initial and follow up vaginal swab (overall AVF, and intermediate vs. bacterial vaginosis) and urine tests (normal, intermediate asymptomatic, intermediate symptomatic, and high-burden single growth), and compliance with treatment. For the 10 % sub-sample of women in the control clusters who are randomly selected for the screening and treatment intervention, we will generate a similar set of intervention/coverage related indicators and compare these with those of the larger group of women in the intervention clusters.

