The next stage of analysis will focus on describing the impact of the intervention on the primary and secondary outcomes. The gestational age at birth will be defined for each pregnancy as the number of days between last menstrual period (reported and recorded at enrollment) and the date of the pregnancy outcome. The primary study endpoint is preterm live birth, and thus we will present, in each group, the number of live births born prior to the pregnancy reaching 37 complete weeks (numerator) and the total number of live births (denominator). The preterm “rate” will be estimated as this proportion with a 95 % binomial exact confidence interval. The impact of the intervention will be assessed by estimating the relative risk of preterm live birth and the absolute risk difference using binomial regression models with a log and identity link functions, respectively. The standard error of this estimate will be constructed using generalized estimating equations and a 95 % confidence interval calculated. We will follow a similar analytic approach to estimate live births prior to 34 weeks (by group and with relative risk) and to estimate the average gestational age at birth for live births, for which we will use a linear regression model with an identity link function and GEE to estimate errors.

We will then expand the pool of analyzable pregnancies to include all spontaneous delivery (i.e. late miscarriages and stillbirths, in addition to live births) and follow an identical approach to estimate the impact of the intervention on this broader set of pregnancies. We will estimate stillbirth and neonatal mortality rates (very early: <1 day, early: <7 days, and overall neonatal mortality: <28 days), and compare across the groups using binomial regression models. Other secondary outcomes of interest that will be compared across the groups include early-onset neonatal infection (defined through use of a sign-based algorithm and restricted to the first 7 days of life) and maternal report of infection in the first 7 and 28 days after delivery.

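### As written, the 10% of control mothers who are screened and treated count as controls in the primary comparison, which dilutes the effect by about a tenth and lowers power

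*Protocol article*

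**What the plan says.** The abstract describes the comparator as "the control arm, which provides routine antenatal and postnatal home-based care". The section on the screening and treatment intervention then states that "a random 10 % of mothers enrolled in the control arm are selected to receive the screening and treatment intervention". The purpose given is to check that baseline infection prevalence is comparable between arms. Each community health worker drew a starting number from 1 to 10, and from there every tenth enrolled mother in her area was taken. The section ends: "The sample size was not adjusted for this allocation".

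The outcome definition reads: "The denominator for preterm live birth rates is all live births". Table 2 agrees. The Analysis section reports, by arm, "the number of live births born prior to the pregnancy reaching 37 complete weeks (numerator) and the total number of live births (denominator"). Only one analysis names the 10% sample, and it is descriptive: its infection and coverage measures are set beside those found in the intervention arm. The further analyses listed are adjustment for imbalance and effect modification by age and parity. None of them sets the sample aside.

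**The concern.** The sampled women are treated where needed as well as tested. If they remain in the control group, the control arm becomes a known mixture of nine parts routine care and one part intervention. Both the relative risk and the risk difference then move toward no effect, and collecting more data does not remove the shift. The sample size was set for an undiluted contrast, so power falls as well. Because the women are chosen by enrolment order, they could be left out at little cost, provided the rule is fixed before the final analysis. Deciding whether they are in or out after seeing the results would be a post hoc choice about the primary estimate.

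**Working it through.** **Inputs, all from the section on sample size.** Population preterm proportion 0.20 ("we estimated this to be 20 %, based on our prior data from this population"); infection prevalence 0.15; preterm risk ratio, infected to uninfected, 2.5; reduction among infected women 60%; 80% power; 5% type I error, taken as two-sided because that reproduces the plan; intra-cluster correlation 0.0060; coefficient of variation of cluster size 0.33; 12 clusters per arm.

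**1. Reproduce the plan.**
- Uninfected risk = 0.20/(0.85 + 0.15×2.5) = 0.1633. Infected risk = 2.5×0.1633 = 0.4082.
- Population reduction = 0.15×0.4082×0.60/0.20 = 18.4%, as stated. The intervention rate is therefore 0.1633.
- Individually randomised size (pooled variance under the null, no continuity correction) = 1728 per arm, or 1728/12 = 144 per cluster.
- Design effect = 1 + 0.006×(144 − 1 + 144×0.33²) = 1.95, as stated.
- 1728×1.952 = 3373, and 3365 with unpooled variance. The plan states 3367.
- Enrolment = 2×3367/(0.9×0.9) = 8314, as stated.

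**2. Dilution if the 10% are kept.**
- Control rate = 0.9×0.2000 + 0.1×0.1633 = 0.1963.
- Risk difference = 0.1963 − 0.1633 = 0.0331, against 0.0367. This is a loss of exactly one tenth, whatever the true effect.
- Relative risk = 0.1633/0.1963 = 0.832, against 0.816. Relative reduction = 16.8%, against 18.4%.

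**3. Power.** Power = Φ[(d − 1.96·SE₀)/SE₁], where d is the risk difference, SE₀ uses the pooled rate and SE₁ the two separate rates. Each arm's live births are divided by the design effect of 1.95, so 3367/1.95 = 1727 effective births.
- As planned: (0.03673 − 1.96×0.01312)/0.01311 = 0.84, power 80.0%.
- Kept as controls: (0.03306 − 1.96×0.01307)/0.01306 = 0.57, power 71.6%.
- Left out (control births 0.9×3367 = 3030, effective 1554): (0.03673 − 1.96×0.01345)/0.01349 = 0.77, power 77.9%.

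**4. Range.** The abstract plans 10,000 women, which gives 10,000×0.81/2 = 4050 live births per group. All rows use design effect 1.95.

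| Scenario | No sample taken | Sample kept as controls | Sample left out |
|---|---|---|---|
| 3367 per group, 18.4% reduction | 80.0% | 71.6% | 77.9% |
| 4050 per group, 18.4% reduction | 86.7% | about 79% | 84.9% |
| 3367 per group, 15% reduction | 62.2% | 53.6% | 60.0% |
| 3367 per group, 20% reduction | 86.4% | 79.0% | 84.6% |

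To restore 80% with the women kept, the individually randomised size is 2117 per arm. At design effect 1.95 that is about 4128 live births per group, or 2×4128/0.81 ≈ 10,193 women enrolled.

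**The case against.** The strongest reply is that retention is an inference. The article never says outright that the sampled women stay in the control group, it reports on them separately, and a full protocol or analysis plan not shown here could exclude them. The remark that the sample size was not adjusted fits exclusion equally well. This stands, and the point is conditional on it. A reader might infer that the plan commits to analysing these women as controls, but the text does not go that far. Even so, the article itself creates the contamination, places the women in the control arm and states the primary numerator and denominator without an exception. Retention is therefore the natural reading.

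Second, the effect is modest and conservative. It cannot manufacture a benefit, and at the abstract's 10,000 women power stays close to 80%. This also stands, except that the article does not link the 10,000 to this allocation, and larger enrolment does not remove the bias.

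Third, intention-to-treat might seem to require keeping everyone. That principle guards against selection after randomisation. Here the protocol assigns the intervention by a random start and enrolment order, so exclusion on that basis leaves a representative control sample if the selection was carried out as described. The qualification matters: the worker who enrols knows which mother is the tenth, and workers are not blinded to arm. Clean selection should be checked, not assumed.

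Fourth, the two interim reviews have already taken place, and interim and final analyses are to follow the same protocol. If the interim analyses included these women, a change needs to be explained.

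**Conclusion.** The point holds in conditional form. If the primary comparison is run as written, about a tenth of the risk difference against routine care is lost (3.67 to 3.31 points; relative risk 0.816 to 0.832). Power is about 72% at the stated 3367 live births per group, not 80%, or about 79% with 10,000 women enrolled. If the women are left out, there is no dilution and power is about 78% (about 85% at 10,000).

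These figures rest on the plan's own rates, infection prevalence and effect among infected women, on its design effect of 1.95, and on sampled women benefiting as much as women in the intervention clusters. A reader might infer a far larger loss of power by also recalculating the design effect from the actual cluster size. That is a separate question about the sample-size section, and such a loss should not be attributed to the 10% sample. Nor do the documents support reading this as a threat to the validity of a positive result, because the bias runs toward no effect.

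**What to change.** - In the Analysis section, define the primary control group as women in control clusters who were not selected for the 10% sample. Exclude by selection (random start and enrolment order), never by whether screening or treatment was received or by test result.
- Report the comparison of all enrolled women as a sensitivity analysis.
- Compare selected and unselected control women at baseline, because the enrolling worker could foresee selection.
- State which population the interim reviews used, and note any difference from the final analysis.
- Restate the power in the sample-size section to match: about 78% at 3367 live births per intervention group and 3030 per control group, or about 85% at 10,000 enrolled.

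The cost is a short change of text and about 337 control births (10% of 3367) lost from the primary comparison, which is about 2 points of power. Keeping the women costs about 8 points at the same enrolment. No new data are needed and no woman's care changes.
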